Esketamine has irreplaceable advantages in maintaining autonomous respiration and sympathetic nervous system-like characteristics. Compared with the combination of opiates and propofol, the combination of ketamine and propofol is preferable, because the latter may increase the possibility of respiratory depression. Esketamine, the d-enantiomer of ketamine with pharmacological actions similar to ketamine’s actions and twice its action intensity provides high clearance rates and low possibility of adverse reactions, which are dose dependent [12]. Small doses of esketamine (recommended dose = 0. 15 mg/kgp [13]) can reduce tussis occurrence with good tolerability. In addition to its role in antagonising NMDAR (the n-methyl-d-aspartate receptor) widespread in the airway, throat, and lungs, esketamine directly acts on airway smooth muscles to expand bronchi through voltage-dependent L-type calcium channel and thus prevents and represses tussis reflection [14]. However, the sympathomimetic action of esketamine contributes to the transient increase in blood pressure and heart rate, whose superimposition with the endoscope insertion–stimulated sympathetic reflex exerts additional burden on the heart and is detrimental to patients with potential myocardial ischaemia [15]. However, when used in combination with propofol, esketamine can not only abolish the suppressive action of propofol on circulation and breathing but also lead to a decrease in propofol doses; thus, esketamine became increasingly popular in clinics [13]. Considering the previously reported evidence about these complementary effects of esketamine as an adjunct to propofol, the combined use of esketamine and propofol may be a promising approach that could reduce the risk of oversedation of propofol in gastrointestinal endoscopy.

Intravenous administration of lidocaine blocks the Na^+^ channel on the sympathetic cell membrane and inhibits the function of the sympathetic adrenal system, transduction of neural signals, and tracheal mechanical stimulation of the function of mucosal sympathetic receptors to prevent tussis reflection. Considerable studies have validated the efficacy of the intravenous injection of 1–2% lidocaine in anaesthesia during upper GI endoscopy; however, the myocardial depression and high individual risks of anaesthetic toxicity necessitate further explicitness of security in applications.

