### Assessments

The pain intensity, cognition function, insanity, anxiety, and depression in the patients will be assessed using a standardised and validated questionnaire. Before enrolment, the patients will be treated in anaesthesia evaluation clinics and screened according to the inclusion criteria and informed consent (Additional file 1). The demographic characteristics of the patients (age, gender, height, weight, medical history, medication history, allergy history, ASA grade, and sleep condition) will be collected, and physical characteristics, blood pressure, heart rate, and oxygen saturation of blood will be measured and recorded as Tbase. Preoperative examinations (urinalysis, haematological examination, and electrocardiogram) will be conducted to validate cardiac, liver, kidney, and coagulation functions. Pain intensity will be evaluated using the numerical rating scale. Anxiety and depression will be assessed using hospital anxiety and depression scale (HADS). Cognition function was assayed through mini-mental state evaluation (MMSE).

On the day of the operation, the vital signs, including blood pressure, heart rate, pulse oxygen saturation, and respiratory rate, will be measured and recorded when the patient entering the operating room and after induction and endoscope entrance, Afterwards, these signed will be recorded every 3 min until the patient left the room. The drug doses of anaesthesia, administration route, anaesthesia time, operation type, operation time, times of biopsy, infusion quantity, blood loss, and satisfaction of endoscopist (satisfied, average, or dissatisfied) will be documented. The vital signs of the patients in the recovery room will be recorded after every 5 min. MMSE scores will be re-evaluated before the patient leaves the recovery room, and the patients will be asked about their satisfaction degree (satisfied, average, or dissatisfied) and the operation and pain severity (0 point represents absolute no pain; 10 points denote unbearable pain). The incidence of adverse events (dizziness, headache, cardiopalmus, dyspnoea, mobility, nausea, and vomiting) will be followed up through phone calls after 0.5 h, 2 h, 1 day, 2 days, 3 days, 1 week, 1 month, and 6 months of the operation. The information about sleep conditions will be collected, and the alterations of MET scores, MMSE scores, HADS scores (the details of any specific manifestations will be inquired) will be assessed.

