### Endpoints

The primary endpoints include the frequency of tussis, nausea and vomiting, and/or body movements observed at the insertion of the endoscope into the pharyngeal cavity or within 5 min of endoscope insertion. Secondary endpoints are as follows: (1) the time of the addition of the first drug, from the end of induction to the addition of the first drug (from the injection of the study medication to the disappearance of eyelash reflex); (2) the time of recovery from anaesthesia, from the end of the operation till the patient left the recovery room (the end of operation to consciousness return); (3) perioperative propofol doses; (4) incidence of perioperative adverse events, including tachycardia, oxygen desaturation (the time of 90% ≤ SpO_2_ < 95% for more than 10 s), breathing inhibition (the time of SpO_2_ < 95% for more than 15 s), bradycardia (< 50 beats per minute or a decrease in HR of 20% or more from baseline), and high and low blood pressure (blood pressure < 30% of the basal blood pressure or systolic blood pressure or blood pressure > 30% of the basal blood pressure); (5) incidence of postoperative adverse events (within 6 months after the operation) including nausea, vomiting, increased secretion, dizziness, over sedation, infection, nightmare, uneasiness, itching, disorientation, insanity, breathing inhibition, diplopia, diarrhoea, intestinal obstruction, urinary retention, gastroesophageal reflux, constipation, shiver, and hallucination; (6) MMSE scores, MET scores, and sleep condition after 0.5 h, 2 h, 4 h, 1 day, 2 days, 3 days, 1 week, 1 month, and 6 months of the operation; (7) pharmacoeconomic outcomes (calculated incremental cost-effectiveness ratio based on cost-effectiveness analyses).

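### Secondary endpoint (5) counts common symptoms over 6 months with no early window or new-onset rule, which dilutes an early drug effect on those items; endpoint (6) schedules sleep before any postoperative night

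*Protocol article*

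**What the plan says.** The Endpoints section of the protocol article defines secondary endpoint (5) as "incidence of postoperative adverse events (within 6 months after the operation) including nausea, vomiting, increased secretion, dizziness". The list has twenty items and ends with "diarrhoea, intestinal obstruction, urinary retention, gastroesophageal reflux, constipation, shiver, and hallucination". It mixes acute sedation effects (over sedation, disorientation, shiver, hallucination) with everyday or gastrointestinal complaints (nausea, vomiting, dizziness, infection, diarrhoea, reflux, constipation). The endpoint sets no early window and does not require an event to be new, worsened or drug-related.

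Endpoint (6) puts three measures on one schedule: "MMSE scores, MET scores, and sleep condition after 0.5 h, 2 h, 4 h, 1 day, 2 days, 3 days, 1 week", followed by 1 month and 6 months. That makes nine time points.

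Under Assessments, adverse events "will be followed up through phone calls after 0.5 h, 2 h, 1 day, 2 days, 3 days, 1 week, 1 month, and 6 months". These are eight calls, with none at 4 h. The symptoms named for the calls are fewer and different: "The incidence of adverse events (dizziness, headache, cardiopalmus, dyspnoea, mobility, nausea, and vomiting". Baseline data include "medical history, medication history, allergy history, ASA grade, and sleep condition", but no baseline record of the endpoint (5) symptoms is stated.

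The Adverse events section has investigators judge the relationship of events to the intervention. Endpoint (5) does not use that judgement.

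**The concern.** Under Intervention, the study injection is given once before the examination, although propofol may be topped up. For esketamine the Introduction itself says that it "provides high clearance rates and low possibility of adverse reactions, which are dose dependent". Drug effects of interest should therefore appear early. The population is having elective upper GI endoscopy, so nausea, vomiting or reflux may well be present before the procedure and recur after it, and an episode of infection, diarrhoea or dizziness within 6 months is unremarkable. A single 6-month incidence for such an item adds these background events to any early drug effect.

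The Discussion presents the trial as evidence on the safety as well as the efficacy of esketamine. If an early excess of, say, nausea or dizziness exists, a 6-month count is a poor way to see it.

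Endpoint (6) has a related timing fault. Assuming that these elective procedures are done by day, no night has passed at 0.5, 2 or 4 h. An answer about sleep then describes either the night before, which baseline already covers, or residual sedation.

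**Working it through.** **The plan's own figure.** There is none to reproduce. The Sample size calculation concerns tussis and propofol demand, and no rate or power is stated for endpoint (5).

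**Inputs from the document.** 100 patients per arm (400 at 1:1:1:1); two-sided tests at 0.05.

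**Inputs assumed.** Early incidence of one symptom of 20% in one arm and 5% in another; a background 6-month incidence b of 0 to 50%, equal in both arms and independent of the early event.

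**Step 1, observed 6-month incidence.** A patient counts if either kind of event occurs:

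p* = 1 − (1 − p)(1 − b) = p + (1 − p)b

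Subtracting the two arms gives p1* − p0* = (p1 − p0)(1 − b).

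With b = 30%: p1* = 0.20 + 0.80 × 0.30 = 0.44; p0* = 0.05 + 0.95 × 0.30 = 0.335; difference 0.105 = 0.15 × 0.70.

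**Step 2, power.** Normal approximation for two proportions, pooled variance under the null:

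power = Φ{[(p1* − p0*) − 1.96 × SE0] / SE1}

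With b = 30%: the pooled rate is 0.3875, SE0 = √(2 × 0.3875 × 0.6125 / 100) = 0.0689, and SE1 = √[(0.44 × 0.56 + 0.335 × 0.665) / 100] = 0.0685. Then (0.105 − 1.96 × 0.0689) / 0.0685 = −0.44, so power is 0.33.

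**Step 3, results.**

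| Background b | Observed rates | Difference | Risk ratio | Power, 100 per arm | N per arm for 80% power |
|---|---|---|---|---|---|
| 0 | 20% vs 5% | 15 points | 4.0 | 90% | 76 |
| 10% | 28% vs 14.5% | 13.5 points | 1.93 | 65% | 143 |
| 30% | 44% vs 33.5% | 10.5 points | 1.31 | 33% | 337 |
| 50% | 60% vs 52.5% | 7.5 points | 1.14 | 19% | 686 |

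With a smaller early effect, 15% vs 5%, power is 66%, 37%, 17% and 11% for the same four backgrounds.

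The first row is also the answer for an item with almost no background: it loses almost nothing from the long window.

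**Step 4, schedules side by side.** Endpoint (6) has time points at 0.5 h, 2 h, 4 h, 1, 2 and 3 days, 1 week, 1 month and 6 months. The calls are at the same times without 4 h. Three of the nine sleep time points come before the first postoperative night, and one of those three has no scheduled contact. Reflux, constipation, diarrhoea and infection appear in endpoint (5) but not among the symptoms named for the calls.

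**The case against.** The strongest reply is that endpoint (5) is a list, not a declared composite, and that reporting each item separately is a natural reading. This stands. A reader might infer that background disease hides every drug effect, or that reflux at month 5 counts the same as hallucination at 30 minutes. Neither is supported. Under item-by-item reporting reflux cannot dilute hallucination, and acute sedation effects should have little background (an assumption). The dilution is confined to the common items.

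Second, the planned data already permit much of the repair. Adverse events are followed at eight separate times, investigators judge causality, and perioperative events are a separate endpoint (4). This also stands, but none of it is built into endpoint (5). Grouping events by period can be left to an analysis plan; here, however, the protocol itself states the 6-month window, so the point concerns a choice made, not a detail left out.

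Third, all event rates in the calculation are assumed. That is true: the direction follows from the algebra, while the size depends on rates that the document does not give.

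Fourth, randomisation balances background between arms. It does, so background events alone create no false difference. They still shrink the absolute early effect by 1 − b and add variance. One might go further and predict a wrong claim of equal tolerability, but the plan describes tests of difference and announces no equivalence conclusion.

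Finally, one might extend the timing criticism to the early MET scores. The article does not define MET, so that cannot be judged.

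**Conclusion.** The point holds in a limited form. For the common symptoms in endpoint (5), a 6-month incidence without a new-onset or worsening rule dilutes an early drug effect. Under the assumed 20% vs 5% at 100 per arm, power drops from 90% to between 65% and 19% for backgrounds of 10% to 50%. This rests on the assumed rates, on independence of early and background events, and on reading the endpoint as any occurrence within 6 months, which is the natural reading although the article does not use the word cumulative. Low-background items are barely affected.

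Sleep at 0.5, 2 and 4 h cannot measure postoperative night sleep, and the 4 h point does not match the call schedule. Later sleep assessments remain usable. Both matters concern secondary endpoints and leave the primary comparison untouched.

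**What to change.** 1. In endpoint (5), make the main safety comparison new or worsened events, item by item, in a prespecified early window built from the calls already scheduled, for example to 3 days or to 1 week. The document gives no basis for preferring one of these; what matters is that the choice is made before unblinding.
2. Ask the same symptoms once at the existing baseline visit, and use the same list at the calls.
3. Report later events to 6 months separately, as descriptive follow-up.
4. In endpoint (6), start postoperative sleep at 1 day, and reconcile the 4 h point with the Assessments section, which has no 4 h call.

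The cost is endpoint wording, one short set of baseline questions and an aligned call list; three sleep assessments per patient are dropped. The downside is small: late events leave the main comparison but are still collected and reported. If recruitment has already closed, the baseline questions can no longer be added, but the split by period can still be fixed before unblinding, with medical history as a partial substitute for judging what is new.

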### Adverse events

In this study, a serious adverse event is defined as any of the following conditions: death, a life-threatening adverse event, inpatient hospitalisation or prolongation of existing hospitalisation, a persistent or significant incapacity or organ damages, a congenital anomaly/birth defect, and a significant medical event that requires intervention. The relationship between the adverse event and intervention will be determined and summarised by the investigators. Adverse events will be treated and reported to the institutional review board (IRB) as soon as possible. Study interventions will be treated for free. The trial will be terminated immediately in case of serious life-threatening events leading to prolonged hospital stay or death.

### Statistical methodology

Efficacy assessment is based on the intention-to-treat (ITT) population, which is defined as all randomised patients. Safety analyses will be performed in a safety evaluation set, which is a subset of all the patients exposed to a minimum of one dose of the studied medication. The SPSS 24.0 software will be used for statistical analyses. Significance will be analysed using two-sided tests, and *p* < 0.05 will be judged as the statistical significance standard. The normally distributed measurement data are presented as mean ± standard deviation (*x* ± *s*). The quartile method will be used to explain the measurement data with non-normal distribution. The repeated analysis of variance and Turkey test will be used for comparisons within a group and between multiple groups, respectively. Count data will be analysed using non-parametric tests, such as Rank-sum test, chi square test, and Fisher exact test. The multivariate regression analysis will be employed to explore the effects of different analgesic drugs combined with propofol on tussis during upper GI endoscopy. We will consider performing predefined subgroup analyses on the primary endpoints according to age, operation types, and special populations. Missing data will not be imputed. In addition, the primary endpoint analysis will also be conducted in a per-protocol set and compared with the ITT analysis to analyse sensitivity. No interim analyses are planned.

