**Discussion:**

Esketamine can reduce tussis occurrence with good tolerability and relax the bronchus and also provides high clearance rates and low possibility of adverse reactions. We aim to demonstrate that the combination of esketamine with propofol for sedation in patients subjected to upper GI procedure is nevertheless superior to only administration of propofol or a combination of propofol with other anaesthetics, such as opioids or lidocaine.

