### Sample size calculation

Based on the results of previous pretest, we speculated that compared with only propofol, the combination of small doses of esketamine with propofol could exhibit significant effect against tussis reduction incidence by a minimum of 15% during upper GI endoscopy. The type I error probability, power of test, and sample size ratio will be set to 0.05, 0.8, and 1:1, respectively. According to relevant literature reports, some believe that a sample size of 18 patients per group will provide 80% of the ability to detect differences between groups 15% difference at a level of *α* = 0.05. At *α* = 0.05, based on the 80% power difference of 15% difference in propofol demand between the levels and detection groups, the power was increased 90%, and the value [200 (109) vs.128 (53)] was added to the sample size calculation formula (*n* = 2*[(*α* + *β*) *σ*/*δ*]^2). The sample size will be estimated by considering a sample loss rate of 10%. Then, the sample size was obtained.

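### Three superiority aims for esketamine share one flat two-sided 0.05 rule on a count primary endpoint, with no primary contrast, order or adjustment, and no contrast is shown to be powered on that endpoint

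*Protocol article*

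**What the plan says.** The Discussion paragraph of the Abstract gives the confirmatory aim: esketamine with propofol is to be shown "superior to only administration of propofol or a combination of propofol with other anaesthetics, such as opioids or lidocaine". With the four arms P, P+S, P+K and P+L randomised 1:1:1:1 at 100 each, that is three contrasts joined by "or".

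The Endpoints section defines the primary endpoint as a frequency of tussis, nausea and vomiting, and/or body movements, so it is count data.

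Statistical methodology sets one threshold for all tests: "Significance will be analysed using two-sided tests, and *p* < 0.05 will be judged as the statistical significance standard". For this type of outcome it says: "Count data will be analysed using non-parametric tests, such as Rank-sum test, chi square test, and Fisher exact test". The only multiple-comparison procedure named, the Tukey test, stands beside repeated analysis of variance. A multivariate regression is to explore drug effects on tussis. The section names no main comparison and no sequence.

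Sample size calculation states an expected effect on tussis for one pair only: "compared with only propofol, the combination of small doses of esketamine with propofol". Its error settings are those of a two-group design: "The type I error probability, power of test, and sample size ratio will be set to 0.05, 0.8, and 1:1, respectively". The values then entered in the formula, 200 (109) versus 128 (53), are introduced as propofol demand, and "the power was increased 90" per cent.

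**The concern.** The stated aim gives one drug three chances at a superiority claim, and the stated rule lets each chance be taken at the full 5%. Nothing in the analysis section says which contrast decides the trial. A result below 0.05 on any one of the three could be reported as the success the Abstract looks for, and that claim would not carry the 5% error rate the plan implies. The closing part of the Discussion looks to the trial to select the best sedation regimen, so the contrasts with P+S and P+L matter as much to readers as the one with P. Those two have no stated effect size and no power statement, so a non-significant result there would carry little information.

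**Working it through.** **Inputs from the protocol article.** Two-sided alpha 0.05 (Statistical methodology). Four arms, 1:1:1:1, 100 each (Study design; Randomisation and blinding). Three P+K superiority contrasts (Abstract, Discussion). Means and SDs 200 (109) and 128 (53), power 0.80 and then 90%, 10% loss (Sample size calculation). No event rate is given anywhere.

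**1. The plan's own sample size.** The formula is n = 2[(z_alpha + z_beta)·sigma/delta]², with delta = 200 − 128 = 72.
- Root-mean-square SD: sqrt[(109² + 53²)/2] = 85.7.
- Two-sided 0.05, 90% power: 2[(1.960 + 1.282) × 85.7/72]² = 29.8, so 30 per group, or 34 after 10% loss (30/0.9 = 33.3).
- With the larger SD of 109: 49 per group, or 55 after loss.
- At 80% power: 23 (26 after loss) and 36 (40 after loss).

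No variant tried with these values gives 100 per group, and the variable is propofol demand. The calculation therefore supports no contrast on the primary endpoint.

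**2. Error rate for the three P+K contrasts, no true differences.** With equal arms and a normal approximation, each statistic is z_j = (Z_K − Z_j)/√2. The three share the P+K arm, so any two have correlation 0.5.
- Independence would give 1 − 0.95³ = 14.3%.
- Simulation with the shared arm (1,000,000 draws): at least one |z| > 1.96 in 12.5%.
- Counting only errors that favour esketamine: 6.3%, against 2.5% for one two-sided test.
- Chi-square tests on simulated binomial data at 100 per arm, assumed common rates 10% to 50%: 12.9% to 13.9%.
- All six pairs: 20.2% (normal), 20.8% to 22.3% (binomial).

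**3. If a four-group chi-square came first.** With no differences anywhere, requiring the overall test to be significant would bring the three-contrast error down to about 4%. If P is truly worse and the three combinations are equal, the overall test is usually passed. The chance of a false difference between P+K and P+S or P+L is then about 9% (simulated 0.091). The plan states no such gate.

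**4. Power for the active-comparator contrasts (all event rates are assumptions).** Power = Φ{[|p1 − p2|√n − z·√(2p̄(1 − p̄))]/√[p1(1 − p1) + p2(1 − p2)]}, with n = 90 (100 less 10% loss) and 15% events under P+K. For a comparator rate of 20%, p̄ = 0.175, giving [0.474 − 1.96 × 0.537]/0.536 = −1.08 and power 0.14.

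| Assumed comparator rate | Power at 0.05 | Power at 0.025 (first Holm step) |
|---|---|---|
| 20% | 0.14 | 0.09 |
| 22.5% | 0.25 | 0.17 |
| 25% | 0.39 | 0.29 |
| 30% | 0.68 | 0.57 |

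**5. The remedy.** With one gate at 0.05, the error under no effect is 5%. If P differs and the three combinations are equal, Holm on the two active contrasts gives about 4.6% (simulated 0.046), within 5%.

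**The case against.** The strongest objection is that a journal article condenses the plan, and contrast order and multiplicity may be set in an analysis plan not shown here. The article also does not list the pairwise tests. That each is judged at 0.05 follows from the single threshold, not from an explicit statement, and the chi-square could be a four-group test. The second part stands as a caution about wording. It does not remove the point, because the article does more than stay silent. It sets a significance rule, assigns tests by data type, names a multiple-comparison method for measurement data and none for counts, and states three superiority aims. Followed as written, that rule gives the error rates above.

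It is also fair that the sample size section singles out P+K versus P and that the Background stresses esketamine. Neither makes that contrast the primary one in the analysis section. If all three superiorities had to be shown together, no adjustment would be needed, but the aim is worded with "or".

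Four stronger readings are tempting and are not supported.
- A reader might treat 12.5% as the rate of false claims for esketamine. It counts both directions; the favourable rate is 6.3%.
- A reader might take the three components as separate primaries, which would raise the error to about 29–33% for three contrasts and 44–49% for six pairs. The Endpoints section uses a plural, but the Intervention section speaks of a single primary outcome and both join the components with "and/or". Those figures should not be used as the size of the problem.
- A reader might conclude that P+K versus P was properly sized and only the others were not. The formula uses propofol demand, so this contrast is not shown to be sized on the primary endpoint either.
- A reader might infer a planned equivalence claim. None is stated; misreading a null result is a risk to guard against.

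**Conclusion.** The point holds. The stated decision rule does not protect the stated claim: error is about 12.5% across the three P+K contrasts, or about 6.3% in esketamine's favour against 2.5% for a single test, and about 20% if all six pairs are tested. These figures assume no true differences, equal arms and unadjusted pairwise testing at 0.05. An unstated overall gate would lower the figure under no effect but would leave about 9% for the two active contrasts if only P differs. Separately, no contrast, least of all those with P+S and P+L, is shown to be powered on the primary endpoint. How low the power is cannot be settled from the document, because every figure for it rests on assumed event rates.

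**What to change.** In Statistical methodology:
- Declare P+K versus P, on the primary endpoint as defined in the Endpoints section, the single primary comparison at two-sided 0.05.
- Only if it is significant, test P+K versus P+S and P+K versus P+L with Holm at 0.05 (smaller p-value against 0.025, the other against 0.05), or in a fixed order with the reason given.
- Report P+S versus P, P+L versus P and P+S versus P+L as risk differences with 95% confidence intervals. If the first two are to be claimed, since the Background hypothesises that each combination reduces tussis, put them in the Holm family as well. It then has four members and the smallest p-value is judged against 0.05/4 = 0.0125.
- Limit superiority conclusions to contrasts that pass, and state that a non-significant active comparison is not evidence of equivalence.
- Label any power figure for these contrasts as resting on assumed event rates.

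The cost is a paragraph of text and no extra patients, and P+K versus P keeps the full 0.05. The price is that the active-comparator claims are lost if the first test fails, and their power is somewhat lower under Holm (for example 0.57 instead of 0.68 at assumed rates of 15% and 30%). The change should be dated before unblinding. If the data are already unblinded, state the limitation and restrict the claim accordingly.
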